### **3.4 Interpretation PCR results**

Genotyping of the recurrent infection will be done by characterizing MSP1, MSP2 and GLURP, single-copy genes in the *Plasmodium falciparum* genome. PCR-amplification of DNA from a single parasite clone results in a single amplification product. For the three genes, each PCR-amplification product of a different size is considered to originate from a different clone of *Plasmodium falciparum* and reflects a different genotype. For the samples collected from the same patient at day 0 and day of recurrent parasitaemia, the length polymorphism of MSP1, MSP2 and GLURP will be determined, i.e. the number of bands in each PCR reaction and their respective size. Results will be interpreted as follows:

**Recrudescence:** For each marker (MSP1, MSP2 and GLURP), at least one identical length polymorphism is found in the sample collected at day 0 and day of recurrent parasitaemia.

**New infection:** For at least one marker, length polymorphism is different between the sample collected at day 0 and that at day of recurrent parasitaemia.

**Indeterminate:** Samples that failed to produce a result due to an inability to amplify DNA at day 0 and/or day of recurrent parasitaemia.

### **3.5 Sample size**

Sample size is estimated according to the expected efficacy at day 28 after treatment as in Africa there is no information beyond this point. Efficacy of each study treatments is likely to be at least 90%. A sample of 155 children per arm will be able to show, in each site, at the 5% significance level with 90% power, that the difference in efficacy between treatments is not more than 10%. Allowing for a loss to follow-up around 10%, the final sample size per arm will be 170 children. Moreover, when combined, the studies will be able to detect a significant difference in efficacy between treatments of 4-6% and major adverse events occurring at the frequency of at least 1-2%.

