### 3.2 Primary Endpoint

There will be several primary end points:

1. PCR unadjusted treatment failure up to day 28 (TF28U): all treatment failures detected during the first active follow up, regardless of genotyping.
2. PCR adjusted treatment failure up to day 28 (TF28A): all early failures before day 14 plus the recurrent parasitaemias detected at day 14 or later and classified by genotyping as recrudescence.

The TF is defined according to the WHO criteria (WHO 2003) as the sum of early\* and late\*\* treatment failures.

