### **3.6 Statistical analysis**

Since the trial has been powered for equivalence at each site, interim analyses will be undertaken for each of the sites separately. Interim analyses will be undertaken by the trial statistician and presented to the DSMB every 6 months during recruitment while safety monitoring will be continuous. A detailed analysis plan will be drawn up prior to the first interim analysis.

For each analysis, both an intention-to-treat, a per-protocol and a CACE approach will be adopted. Patients in each treatment group in each site will be described separately with respect to baseline characteristics. The clinical importance of any imbalance will be noted though statistical tests of significance will not be undertaken.

For the analysis at each site, and for the primary outcomes relating to treatment failure, the relative treatment effect will be summarised in terms of the risk difference and associated confidence interval for each pairwise combination of treatments.

For the combination of data across sites, a meta-analytic approach will be employed. The six pairwise comparisons of treatments will be undertaken, stratified by site. Heterogeneity due to patient-level and site-level characteristics will be investigated. Finally, all data will be entered into a regression model and a network meta-analytic approach adopted.

If appropriate, logistic regression will be used to examine the effect of prognostic factors on the primary outcome. Tests of interaction between baseline characteristics and treatment will be kept to a minimum.

Adverse events will be grouped according to a pre-specified side-effect coding system and tabulated. The number (and percentage) of patients experiencing each adverse event will be compared across treatment groups. The number (and percentage) of occurrences of each adverse event will also be compared across treatment groups.

Every effort will be made to minimise the amount of missing data in the trial. However it is realistic to assume a priori that missingness may be informative. Whenever possible, information on the reason for missing data will be obtained. Sensitivity analyses, including imputation, will be undertaken to assess the robustness of the conclusions to the missing data.

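### At 90% efficacy, 155 children per arm gives 90% power for a one-sided non-inferiority comparison, but only about 80% for the site-level equivalence named in the protocol

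*Protocol*

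**What the plan says.** Section 3.5 (Sample size) starts from the planning assumption "Efficacy of each study treatments is likely to be at least 90" percent. From this it derives 155 evaluable patients in every arm as enough for any single centre to demonstrate, "at the 5% significance level with 90% power, that the difference in efficacy between treatments is not more than 10" percent. It does not say whether the 5% is one-sided or two-sided, gives the margin no direction and names no endpoint. After an allowance of around 10% for loss to follow-up, enrolment is 170 per arm.

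Section 3.6 (Statistical analysis) names the hypothesis: "Since the trial has been powered for equivalence at each site". It gives this as the reason for doing interim analyses site by site. The site-level analysis of the primary outcomes is "the risk difference and associated confidence interval for each pairwise combination of treatments". No reference treatment is named and no confidence level is given.

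Section 3.2 says "There will be several primary end points": PCR-unadjusted failure to day 28 (TF28U) and PCR-adjusted failure to day 28 (TF28A). Section 3.5 gives one efficacy figure and does not say which of the two it describes.

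**The concern.** A margin without direction, comparison of every pair without a reference arm, and the word equivalence all point to a two-sided requirement: the interval for the difference must lie wholly within ±10 points. The type II error then arises at both limits. A sample size that allows for it at one limit only overstates the power.

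If the label and the number do not match, each site is presented as having a 10% chance of missing true equivalence when, at the planning value, the chance is about 20% or more. A site-level interval that crosses ±10 could then be read as a sign of a real difference when limited precision explains it. The claim also supports the choice to run interim analyses by site.

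**Working it through.** **Inputs from the protocol.** Efficacy 0.90 in both arms, true difference 0, margin 0.10, 5% level, 90% power, 155 evaluable per arm (section 3.5); equal allocation of 170 per arm (sections 3.1 and 3.5); equivalence (section 3.6). Variance term: 2 × 0.9 × 0.1 = 0.18, and 0.18 / 0.10² = 18.

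**Step 1: reproduce 155.** One-sided 5% non-inferiority with 90% power:

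n = (z₀.₉₅ + z₀.₉₀)² × 18 = (1.645 + 1.282)² × 18 = 154.1 with unrounded z values, so 155.

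This matches exactly. Other designs with 90% power do not:

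| Design | n per arm |
|---|---|
| Non-inferiority, one-sided 5% | 155 |
| Non-inferiority, one-sided 2.5% | 190 |
| Equivalence, 90% interval: (1.645 + 1.645)² × 18 = 194.8 | 195 |
| Equivalence, 95% interval: (1.960 + 1.645)² × 18 = 233.9 | 234 |
| Superiority, 90% v 80%, one-sided | 217 |
| Superiority, 90% v 80%, two-sided | 266 |

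The equivalence formula with a 90% interval does return 155, but at 80% power.

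**Step 2: equivalence power at the planned size.** Power = 2Φ(0.10/SE − z) − 1, with SE = √(0.18/n).

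- n = 155: SE = 0.03408 and 0.10/SE = 2.934.
  - 90% interval: 2Φ(2.934 − 1.645) − 1 = 2(0.9014) − 1 = 80.3%.
  - 95% interval: 2Φ(2.934 − 1.960) − 1 = 2(0.8351) − 1 = 67.0%.
- n = 153 (170 × 0.9): 79.6% and 66.1%.
- n = 170 (no loss): 84.7% and 73.4%.

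Exact binomial enumeration of Wald intervals at n = 155 gives 80.5% and 66.7%, so the normal approximation is adequate.

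**Step 3: sensitivity to the lower bound.** Equivalence power at 155 per arm, no true difference:

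| Efficacy in both arms | 90% interval | 95% interval |
|---|---|---|
| 90% | 80.3% | 67.0% |
| 92% | 89.0% | 80.1% |
| 95% | 98.3% | 96.2% |

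The efficacy p at which 155 gives 90% equivalence power solves 2p(1 − p)(z + 1.645)²/0.01 = 155.

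- 90% interval: p(1 − p) = 1.55/(2 × 10.82) = 0.0716, so p is about 92.2%.
- 95% interval: p(1 − p) = 1.55/(2 × 12.99) = 0.0597, so p is about 93.6%.

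In the other direction, p(1 − p) grows as efficacy falls from 90% towards 50%, so power drops below the 90% row. Any non-zero true difference also lowers it.

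**The case against.** The best reply is that 90% is a floor. Section 1.1 cites a 95% day-28 response for DHAPQ and efficacy above 90% for AQAS, and at 95% in both arms equivalence power exceeds 96% with either interval. This stands as a limit on the finding: the shortfall applies at the planning value and fades above it. It does not rescue the statement, because 155 reproduces at exactly 90% and the protocol claims 90% power without requiring anything higher.

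Second, the confidence level may be set in the analysis plan, which is not at hand. This also stands in part. The like-for-like figure for a 5% level is the 90% interval, hence 80%; the 67% is conditional on a 95% interval. Neither makes 155 a 90%-power equivalence size at 90% efficacy.

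Third, section 3.6 sets no site-level rule for declaring equivalence. It reports risk differences with intervals, and the cross-site analysis has up to 1360 per arm for one comparison. That limits the practical harm, but the power claim is made for each site.

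Two stronger readings are tempting. A reader might compute the chance that all three pairs at a site are shown equivalent (about 60% with a 90% interval), but the protocol makes no joint claim. A reader might also put a figure on the power for TF28U by assuming 80% or 70% unadjusted efficacy. The protocol gives no such rate, and the transmission intensities in Table 1 range from an EIR of 6 to above 70, so only the direction can be stated.

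**Conclusion.** The concern holds at the planning value. With 90% efficacy in both arms and no true difference, 155 per arm gives 90% power for one one-sided 5% comparison against a 10-point margin, and 80.3% power for equivalence with a 90% interval (67.0% if a 95% interval is used). At the 153 expected to be evaluable, the figures are 79.6% and 66.1%. The stated 90% for equivalence is reached only from about 92.2% efficacy (90% interval) or 93.6% (95% interval).

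The fault lies in the label, not in the sample-size arithmetic, which is correct for one-sided non-inferiority. A reader might infer that the trial is too small or that its pooled comparisons are affected; this check supports neither inference. The figure of 170 enrolled, against 155/0.9 = 172.2, is close enough not to be a separate issue.

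**What to change.** Reconcile sections 3.5 and 3.6 in one of two ways.

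1. Keep the site-level equivalence objective. Restate the power in section 3.5 as about 80% at 90% efficacy with a 90% confidence interval (about 66–67% if a 95% interval is used), and add the range for higher efficacy: 89.0% at 92% and 98.3% at 95% with the 90% interval.
2. Say that the 90% is the power of each single one-sided 5% comparison against the 10-point margin, and remove the equivalence wording from section 3.6. Relabelling the trial as directional non-inferiority would not be enough: no reference arm is named, and testing both directions within a pair is equivalence again.

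Under either option, state that the figure assumes 90% efficacy and no true difference, and that power is lower for any primary endpoint with lower efficacy, such as TF28U where reinfection is common.

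The cost is a change of wording in two sections and, under the first option, a less favourable stated power. It adds no patients and leaves the endpoints, analysis and conduct unchanged. For comparison, 90% equivalence power at 90% efficacy would need 195 evaluable per arm (90% interval) or 234 (95% interval).

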### **3.6 Statistical analysis**

Since the trial has been powered for equivalence at each site, interim analyses will be undertaken for each of the sites separately. Interim analyses will be undertaken by the trial statistician and presented to the DSMB every 6 months during recruitment while safety monitoring will be continuous. A detailed analysis plan will be drawn up prior to the first interim analysis.

For each analysis, both an intention-to-treat, a per-protocol and a CACE approach will be adopted. Patients in each treatment group in each site will be described separately with respect to baseline characteristics. The clinical importance of any imbalance will be noted though statistical tests of significance will not be undertaken.

For the analysis at each site, and for the primary outcomes relating to treatment failure, the relative treatment effect will be summarised in terms of the risk difference and associated confidence interval for each pairwise combination of treatments.

For the combination of data across sites, a meta-analytic approach will be employed. The six pairwise comparisons of treatments will be undertaken, stratified by site. Heterogeneity due to patient-level and site-level characteristics will be investigated. Finally, all data will be entered into a regression model and a network meta-analytic approach adopted.

If appropriate, logistic regression will be used to examine the effect of prognostic factors on the primary outcome. Tests of interaction between baseline characteristics and treatment will be kept to a minimum.

Adverse events will be grouped according to a pre-specified side-effect coding system and tabulated. The number (and percentage) of patients experiencing each adverse event will be compared across treatment groups. The number (and percentage) of occurrences of each adverse event will also be compared across treatment groups.

Every effort will be made to minimise the amount of missing data in the trial. However it is realistic to assume a priori that missingness may be informative. Whenever possible, information on the reason for missing data will be obtained. Sensitivity analyses, including imputation, will be undertaken to assess the robustness of the conclusions to the missing data.

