### **Statistical analysis**

For the proposed trials each pairwise comparison of treatments will be considered, stratified by site. Heterogeneity due to patient-level and site-level characteristics will be investigated. Finally, all data will be entered into a regression model and a network meta-analytic approach adopted. For each pairwise comparison, both an intention-to-treat, a per-protocol and a Compliance Adjusted Causal Effect (CACE) approach will be adopted. Within each site patients in each treatment group will be described separately with respect to baseline characteristics. The clinical importance of any imbalance will be noted though statistical tests of significance will not be undertaken. For treatment failure, the relative treatment effect will be summarised in terms of the odds ratio and confidence interval, provided no significant unexplained heterogeneity is evident on this scale. If appropriate, logistic regression will be

---

 Lumley T. Network meta-analysis for indirect treatment comparisons. *Statistics in Medicine* 2002; 21: 2313-2324.

used to examine the effect of prognostic factors on this outcome. Tests of interaction between baseline characteristics and treatment will be kept to a minimum. Adverse events will be grouped according to a pre-specified side-effect coding system and tabulated. The number (and percentage) of patients experiencing each adverse event will be compared across treatment groups. The number (and percentage) of occurrences of each adverse event will also be compared across treatment groups. No formal statistical testing will be undertaken.

Every effort will be made to minimise the amount of missing data in the trial. However it is realistic to assume a priori that missingness may be informative. Whenever possible, information on the reason for missing data will be obtained. Sensitivity analyses, including imputation, will be considered to assess the robustness of the conclusions to the missing data.

Interim analyses will be undertaken by the trial statistician and presented to the DSMB every six months during recruitment, i.e. approximately after every 500 patients per group have been entered. A detailed analysis plan will be drawn up prior to the first interim analysis.

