CD is well tolerated in young children and most of the serious adverse events recorded are more likely to be disease-related than drug-related. One percent of patients taking CD and 1% of those taking SP reported serious adverse events, most commonly red blood cell disorders. Dapsone is known to cause methaemoglobinaemia and haemolysis (especially in G6PD deficient people). Clinically significant increases in methaemoglobin were not seen in SP-treated patients, but were observed in 4.2% of those given CD (all mild cases and 1 moderate case, all of limited duration). None of the children showed dyspnoea, the main symptom of high methaemoglobinaemia, and no action was required by attending physicians. Severe hemolysis is of concern because it is a feature of falciparum malaria, making it difficult to identify cases of drug-induced haemolysis. G6PD-deficient children in the CD group were more likely than similar patients in the SP group to have a > 2g/dL haemoglobin drop when compared to those without G6PD deficiency, but by day 14 Hb values in both groups had been restored to baseline. Larger haemoglobin falls after treatment with CD than after SP have been reported previously. Other genetic polymorphisms, such as those in candidate genes responsible for metabolism of CD, are also potential determinants of the risk of adverse events.

Although Lapdap exerts a significantly lower selective pressure than SP (Nzila et al, 2000), and it is currently highly effective, activity will be greatly reduced by the selection of one further DHFR mutation. This mutation, at codon 164 was selected by SP use in both South America and South-East Asia, and has been found at low frequency in Tanzania. The use of CD as monotherapy may therefore increase selective pressure for the 'quadruple DHFR mutant'. Associating CD with artesunate can considerably increase its antimalarial activity and at the same time might delay the selection of the quadruple DHFR mutants. A trial investigating the safety and efficacy of non co-formulated CD and artesunate in children 6-59 months old with uncomplicated malaria is ongoing in Rwanda. Preliminary results show a relatively good efficacy and no major safety problem.

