## **14. ETHICAL ISSUES**

AQ+AS and AL have been successfully used for the treatment of falciparum malaria in Phase III studies though the former in a non-coformulated form. AL is widely used to treat uncomplicated malaria in Africa. DHAPQ has been used for several years in Asia, including safety studies in children. Recent trials in Rwanda and Peru (initiated and followed up by the ITM, Belgium) do not show any specific safety problem^8. The combination is well tolerated. Chlorproguanil-dapsone has been used in young children, it is well tolerated and most of the serious adverse events recorded were more likely to be disease-related than drug-related. Dapsone is known to cause methaemoglobinaemia and haemolysis (especially in G6PD deficiency). Clinically significant increases in methaemoglobin were not seen in SP-treated patients, but were observed in 7% of those given chlorproguanil-dapsone (all mild cases and 1 moderate case, all of limited duration). None of the children showed dyspnoea, the main symptom of high methaemoglobinaemia, and no action was required by attending physicians. Severe hemolysis is of concern because it is a feature of falciparum malaria, making it difficult to identify cases of drug-induced haemolysis. G6PD-deficient children in the chlorproguanil-dapsone group were more likely than similar patients in the SP group to have a  $\geq 2\text{g/dL}$  Hb drop. However, by day 14 Hb values in both groups had been restored to baseline. Larger Hb falls after treatment with CD than after SP have already been reported. There is no reason to think that the addition of artesunate will increase such risk. Nevertheless, children receiving CDA will be carefully monitored and Hb tested every day until day 3 after treatment. If needed, blood transfusion can be rapidly done in all sites where CDA is tested. Moreover, the recruitment of children having an Hb  $\geq 7\text{g/dL}$  guarantees that, even if there is a drop, it will not reach life-threatening values.

The study will be presented for ethical clearance to the local ethical committees where the study is carried out and to the corresponding committees of the northern institutions directly involved in a specific site. Prior to the start of the project, the study will be explained to the communities involved. Written informed consent will be obtained from the guardians for all children before entering the study.

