**TABLE D. Guidelines for Grading of Laboratory Abnormalities**

|                           | Grade 1
MILD | Grade 2
MODERATE | Grade 3
SEVERE | Grade 4
LIFE-
THREATENING |
|---------------------------|-------------------------|-----------------------------|---------------------------|------------------------------------------|
| Haemoglobin (g/dL) | 9.0 – 9.9               | 7.0 – 8.9                   | 5.0 – 6.9                 | < 5.0                                    |

Reference – The Harriet Lane Handbook, 15th edition, 2000†

Reference – WHO Toxicity Grading Scale for Determining the Severity of Adverse Events

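### Section 3.6 runs interim analyses site by site for an efficacy reason, while the synopsis expects about 500 patients per group, which only pooled data can reach; the DSMB's between-arm safety tables would be weak

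*Protocol*

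**What the plan says.** **Interim unit.** Section 3.6 of the protocol: "Since the trial has been powered for equivalence at each site, interim analyses will be undertaken for each of the sites separately". The next sentence has the results "presented to the DSMB every 6 months during recruitment while safety monitoring will be continuous".

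**Interim timing.** The synopsis (Statistical analysis) has the interims presented to the DSMB "every six months during recruitment, i.e. approximately after every 500 patients per group have been entered". It does not mention a split by site.

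**Numbers.** The synopsis and section 3.1 fix 170 patients per arm and 510 per site at 10 sites. Section 3.5 derives this from efficacy, and says that events at a frequency of 1–2% can be detected when the studies are combined.

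**DSMB.** Section 13.2 sets it up for independent advice on safety. It reviews interim reports, is told of every serious adverse event, and may stop the trial or an arm.

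**Haemoglobin.** Section 1.1 reports that G6PD-deficient children given chlorproguanil-dapsone were "more likely than similar patients in the SP group to have a > 2g/dL haemoglobin drop". Section 14 says that recruiting children with Hb of at least 7 g/dL "guarantees that, even if there is a drop, it will not reach life-threatening values". In Appendix I, Table D, Hb below 5.0 g/dL is Grade 4, life-threatening. In Appendix V it is severe anaemia.

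**The concern.** The two descriptions of the interim analyses do not fit together. A look after about 500 per group presupposes data pooled over sites, and section 3.6 says that the looks are made within sites.

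The by-site rule is justified by equivalence power, which bears on treatment failure. It is worded to cover all interim analyses, including those that inform a safety board. Whether a drug causes haemolysis is a question across sites, and the protocol's own safety aim relies on combined data.

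The stake is greatest for CDA. Section 14 names haemolysis as a dapsone risk and notes that malaria itself causes it, so drug-induced cases are hard to identify one by one. That is where a randomised comparison between arms helps. Only known G6PD deficiency is excluded (section 3.9), and G6PD status is determined later from stored samples (sections 3.8 and 3.10.1), so deficient children can be enrolled.

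**Working it through.** **1. The plan's own site size.** Inputs from section 3.5: efficacy 90%, margin 10 points, 5% significance, 90% power.

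n = 2 × 0.90 × 0.10 × (z0.95 + z0.90)² / 0.10² = 0.18 × (1.645 + 1.282)² / 0.01 = 154.1, so 155 per arm.

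This reproduces the stated 155, as a one-sided 5% calculation. Adding 10% gives 155 × 1.1 = 170.5, against the stated 170. The site size therefore comes from efficacy alone.

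**2. Does 500 per group fit a site?** 500 / 170 = 2.9, so at least three sites must be pooled to reach it. From Table 1, CDA is given at six sites, 6 × 170 = 1020 patients. A pooled look at 500 falls at 500 / 1020 = 49% of CDA enrolment, or 500 / 6 ≈ 83 per site if accrual is even (assumed). The gloss is plausible for pooled data and impossible for a site.

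**3. Sites at which CDA is randomised against each comparator (Table 1).**

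| Comparison | Shared sites | Per arm, full enrolment |
|---|---|---|
| CDA vs DHAPQ | 6 | 1020 |
| CDA vs AL | 4 | 680 |
| CDA vs AQ+AS | 2 | 340 |

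**4. How much a between-arm table can show.** The protocol gives no expected rate of haemolysis or severe anaemia, so the rates are assumptions. Power is the sum, over all pairs of counts with more events on CDA and a two-sided Fisher p-value at or below 5%, of the product of the two binomial probabilities.

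| Per arm | What it represents | 1% vs 3% | 1% vs 4% |
|---|---|---|---|
| 85 | one site, half enrolled | 2.0% | 6.1% |
| 170 | one site, full | 12.6% | 28.4% |
| 340 | CDA vs AQ+AS, pooled, full | 36.0% | 65.5% |
| 510 | CDA vs DHAPQ, pooled, half | 57.2% | 86.1% |
| 680 | CDA vs AL, pooled, full | 71.3% | 94.5% |
| 1020 | CDA vs DHAPQ, pooled, full | 88.5% | 99.3% |

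Pooled CDA vs AQ+AS at half enrolment is 170 per arm, the same 12.6% as one full site. The gain from pooling thus depends strongly on the pair.

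A simpler measure is the chance of seeing at least one event at a true rate of 1%, which is 1 − 0.99ⁿ: 57% with 83 patients, 82% with 170 and 99% with 500.

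**5. The section 14 assurance.** A child with entry Hb h ends below 5.0 g/dL if the fall exceeds h − 5.0. For h = 7.0 that is any fall above 2.0 g/dL, the size of fall that section 1.1 reports. For h = 7.5 it would take more than 2.5 g/dL. The claim therefore fails for children at or near the entry limit, by the protocol's own figures.

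**The case against.** A reader might infer that the DSMB would be nearly blind to CDA haemolysis. The documents do not support that. Section 3.6 keeps safety monitoring continuous. Section 7.1.3 requires every serious adverse event to be reported within 24 hours, and life-threatening events are serious. Hb below 5.0 g/dL is Grade 4, life-threatening, in Table D, so such cases should reach the DSMB singly from every site. Section 14 has Hb checked daily to day 3 on CDA, and the DSMB may stop an arm.

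A reader might also take 500 per group as a fixed trigger. It is an approximate gloss, and both places set the same six-monthly rule.

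Nor does it follow that the DSMB cannot detect an excess. One board receives all the site tables and may add them up. The synopsis plans no formal testing of adverse events, so the power figures only illustrate how much information a table carries.

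The by-site sentence can be read as concerning efficacy only, and the detailed analysis plan may add pooled safety tables. This part stands only in part. Section 3.6 sets no such limit, and a plan that pooled the interims would depart from its wording. SAE notification also gives no comparison between arms, and an Hb fall above 2 g/dL need not be serious.

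The section 14 sentence is a separate matter and no defect of the interim rules. Section 14 also cites daily Hb checks and access to transfusion. Neither makes the word for certainty correct.

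**Conclusion.** The point holds as a moderate inconsistency with a practical consequence. It is not a failure of safety oversight. The interim unit in section 3.6 does not fit the synopsis gloss: 500 is 2.9 times the most any site arm can hold. Site-only tables also drop the pooling on which section 3.5 rests its safety claim.

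The loss is confined to between-arm comparison of Hb falls and non-serious haemolysis. Its size depends on the assumed rates and on the pair. At 1% vs 3%, power rises from 13% at one full site to 88.5% for CDA vs DHAPQ, 71% for CDA vs AL, and only 36% for CDA vs AQ+AS, all pooled at full enrolment. At interim looks the pooled figures are lower, for example 57% for CDA vs DHAPQ at half enrolment.

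Separately, the guarantee in section 14 conflicts with section 1.1, Table D and Appendix V.

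**What to change.** 1. In section 3.6, limit the by-site rule to interim efficacy analyses.
2. State there that each six-monthly DSMB report also gives safety pooled over sites and stratified by site, for each randomised pair, with the site tables appended. Contents: serious adverse events and Hb changes from values already measured. At CDA sites Hb is taken on days 1 and 2 in all three arms (Figure 1, footnote 3), and day 3 is routine everywhere.
3. In the synopsis, delete the 500-per-group remark or say that it refers to pooled data.
4. Reconcile the section 14 sentence on entry Hb with section 1.1, Table D and Appendix V. How to do so is for the sponsor and investigators.

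The cost is protocol wording and a DSMB report template. No new data, visits or patients are needed.
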